# Umbilical cord mesenchymal stem (stromal) cells to treat lupus nephritis: protocol for a prospective clinical trial

## Study design

This is a proposed protocol for a prospective clinical trial, developed in accordance with the Standard Protocol Items: Recommendations for Interventional Trials (SPIRIT) checklist. The Affiliated Drum Tower Hospital of Nanjing University Medical School (Nanjing, China) acts as the initiating sponsor and coordinator of this trial. The observed group will receive intravenous infusion of Umbilical cord mesenchymal stem cells (UC-MSCs).

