## Subjects Eligibility

Recruitment methodologies include advertisements in academic media as well as liaisons with general practitioners, rheumatologist.

Inclusion criteria are as follows:

(1) Patients with a documented history of fulfilling at least 4 out of the 11 ACR 1997 SLE classification criteria before randomization; (2) Age between 18 and 65 years at the time of obtaining informed consent; (3) Biopsy-confirmed lupus nephritis with pathological classification of Class III, IV, V, III+V or IV+V (2003 ISN/RPS lupus nephritis histological classification criteria), accompanied by active lesions (activity index ≥ 1 and/or increased chronicity index), within 24 weeks; (4) Urine protein/creatinine ratio > 1.0 or 24-hour urine protein quantification > 1.0 g, with or without active urinary sediment containing red blood cell casts; (5) All subjects receiving concurrent treatment with steroids alone or in combination with antimalarial drugs; (6) Meeting one of the following conditions: a. Never received immunosuppressive agents previously. b. Previously received immunosuppressive agents (including CTX, cyclosporine, TAC, MMF, azathioprine, leflunomide, or sirolimus) but had inadequate response or intolerance to treatment; (7) For women of childbearing potential, a negative serum pregnancy test at screening; (8) Willingness to provide written informed consent and comply with the study protocol requirements and restrictions.

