## Safety indicators and primary and secondary efficacy endpoints

The primary efficacy endpoint of this study is the assessment of the overall response rate (complete response, CR, and partial response, PR) at 24 weeks, defined as a urine protein/creatinine ratio < 0.5, absence of active urinary sediment, and normal serum albumin level. The secondary efficacy endpoints include:

(1) Time to achieve PR and CR in both groups of subjects; (2) Changes in quantified urine protein and/or urine protein/creatinine ratio, serum albumin, serum creatinine, estimated glomerular filtration rate (eGFR), complement levels (C3, C4), autoantibodies (anti-dsDNA, ANA, anti-Smith, anti-RNP, anti-SSA/Ro, anti-SSB/La, anti-phospholipid antibodies) and Coombs test from the screening period to respective follow-up visits; (3) Changes in patient-reported Health Assessment Questionnaire (HAQ) scores and physician's Visual Analog Scale (PhGA-VAS) scores from the screening period to respective follow-up visits.(4) Changes in SLE Disease Activity Index-2000 (SLEDAI-2K), British Isles Lupus Assessment Group-2004 (BILAG-2004) scores, improvement rate in SLE Responder Index from the screening period to respective follow-up visits. (5) Overall response rate (CR + PR) in both groups of subjects at 12 weeks. The safety evaluation includes: (1) Recording of adverse events occurring from the start of subject enrollment until the end of follow-up; (2) Vital sign assessments (blood pressure, pulse, respiratory rate, and temperature) were evaluated every 4 weeks for 24 weeks; (3) Laboratory tests (including complete blood count, urinalysis, liver function, and blood biochemistry) were tested every 4 weeks for 24 weeks.

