## Statistical analysis

Descriptive statistics will be used to summarize baseline characteristics, efficacy outcomes, and safety data. For the safety analysis set, all safety indicators will be obtained from those who have undergone UC-MSC. In the full analysis set, subjects will be excluded if they received no intervention or never gave any evaluation outcome. For the baseline characteristics, continuous variables will be expressed as means ± standard deviations, while categorical data will be given as frequencies. The paired *t*-test will be applied to analyze continuous and categorical variables. For the safety indicators, primary endpoint, and most secondary outcomes, including blood coagulation function, routine tests (blood, urine, and excrement), biochemistry and tumor findings, the paired *t*-test will be used to detect any differences. All statistical analyses will be performed using Statistical Product and Service Solutions (Version 22.0, IBM, New York, NY, USA) by the principal biostatistician. *p* < 0.05 will be considered statistically significant.

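### The paired t-test fixed for the week-24 response rate never compares the groups, and it can credit standard-of-care responses to UC-MSC

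*Protocol*

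**What the plan says.** The section on safety indicators and endpoints makes the primary efficacy endpoint "the overall response rate (complete response, CR, and partial response, PR) at 24 weeks". Response at that visit is "defined as a urine protein/creatinine ratio < 0.5, absence of active urinary sediment, and normal serum albumin level". Each patient either meets this or does not.

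Several places point to a comparison of groups. Subjects Eligibility refers to "fulfilling at least 4 out of the 11 ACR 1997 SLE classification criteria before randomization". The secondary endpoints include "Overall response rate (CR + PR) in both groups of subjects at 12 weeks". The Intervention section says that everyone receives standard of care alongside the intervention assigned to them. Study design, however, describes only one group: "The observed group will receive intravenous infusion of Umbilical cord mesenchymal stem cells (UC-MSCs". No section says what the other group receives.

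On baseline status, Subjects Eligibility requires "Urine protein/creatinine ratio > 1.0 or 24-hour urine protein quantification > 1.0 g".

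The Statistical analysis section assigns the paired t-test to continuous and categorical variables alike. It then names the test a second time, now for the main outcome: "primary endpoint, and most secondary outcomes, including blood coagulation function, routine tests (blood, urine, and excrement), biochemistry and tumor findings, the paired *t*-test will be" applied. It names no between-group test and does not say what is paired with what. The significance level is 0.05, with sidedness not stated.

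**The concern.** A paired t-test needs two linked measurements. Independent randomised patients are not linked across groups, and the protocol describes no matching, so the links can only be within a patient, baseline to follow-up. For a responder endpoint that contrast is nearly empty, because the entry criteria put almost every patient below the response threshold at the start.

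The question then becomes whether some patients respond by week 24. Standard of care alone can bring that about. A significant result would show that patients improved on the whole package of treatment. It would not show that UC-MSC added anything, and the 5% level would not be the error rate for a claim that UC-MSC works.

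This is not a detail left to a statistical analysis plan. The protocol states the test in words, and an analysis plan that named another test would contradict it.

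**Working it through.** **No figure to reproduce.** The protocol gives no sample size, power or effect size.

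**Inputs.** From the protocol: binary outcome at week 24, paired t-test, alpha 0.05. Assumed: two-sided testing, n from 10 to 100 patients in the paired analysis, and background response to standard of care of 10% to 40%.

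**Baseline responder rate.** A patient who enters on a urine protein/creatinine ratio above 1.0 cannot have a ratio below 0.5 at that point, so the rate is exactly zero on that route. A patient who enters only on 24-hour protein above 1.0 g could in theory have a ratio below 0.5, but would also need inactive sediment and normal albumin to count as a responder. The rate on that route is close to zero, not provably zero.

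**The statistic.** Score response as 1 and non-response as 0. With all baselines 0 and r responders among n, the mean difference is r/n and t = √[(n − 1)·r/(n − r)], on n − 1 degrees of freedom.

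| n | t at r = 3 | t at r = 4 | critical t | p at r = 4 |
|---|---|---|---|---|
| 10 | 1.964 | 2.449 | 2.262 | 0.037 |
| 20 | 1.831 | 2.179 | 2.093 | 0.042 |
| 30 | 1.795 | 2.112 | 2.045 | 0.043 |
| 60 | 1.762 | 2.053 | 2.001 | 0.045 |
| 100 | 1.750 | 2.031 | 1.984 | 0.045 |

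For example, at n = 20 and r = 4: √(19 × 4/16) = √4.75 = 2.179. The threshold is 4 responders at every n from 10 to 100.

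**Chance of significance when UC-MSC adds nothing.** This is P(X ≥ 4) for X binomial with size n and the background response rate. At n = 20 and 20%: 1 − (0.0115 + 0.0576 + 0.1369 + 0.2054) = 0.589.

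| n | 10% | 20% | 30% | 40% |
|---|---|---|---|---|
| 10 | 1% | 12% | 35% | 62% |
| 20 | 13% | 59% | 89% | 98% |
| 30 | 35% | 88% | 99% | >99% |
| 40 | 58% | 97% | >99% | >99% |
| 60 | 86% | >99% | >99% | >99% |

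**Sensitivity to baseline responders.** A simulation with an assumed 5% of responders at baseline, independent of week-24 status, gives lower chances at 20% background: 28% at n = 20, 41% at n = 30 and 72% at n = 60. At 30% background they are 55%, 74% and 97%.

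**Two groups that do not differ.** With 30 patients per group and 30% response in each, each group's paired test is significant with probability 0.991. Both are significant with probability 0.991² = 0.98.

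**A between-group test in its place.** With equal response of 20% to 40% in both groups and 20 to 60 patients per group, exact enumeration gives a false-positive rate of 4.8% to 5.3% for the uncorrected chi-square test and 2.2% to 3.2% for Fisher's exact test.

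**The case against.** The strongest reply is that the protocol never says the pairing is baseline against week 24, and it defines no responder status at baseline. The figures above therefore belong to a reading of the text. That is fair. But no other pairing can be built from the document, and the fault that the test does not compare groups does not depend on the figures.

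A reader might infer that the test is bound to be significant with no UC-MSC effect. The documents do not support that. They give neither the number of patients nor the background response. The chance is about 12% at n = 10 with 20% background and 13% at n = 20 with 10%, and it falls further if some patients are responders at baseline.

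A reader might also take it as settled that the trial compares UC-MSC plus standard of care with standard of care alone. Randomisation and two groups are mentioned, but no section describes a control arm, Study design names only the group given UC-MSC, and the safety set covers only patients who received UC-MSC. The comparator is unstated. If there were only one arm, the paired test would still be unable to separate UC-MSC from standard of care.

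Finally, a between-group test has a price in power. For an assumed 30% against 50% response, an unadjusted chi-square test has power of about 25%, 35% and 62% at 20, 30 and 60 per group, and about 93 per group are needed for 80%. This stands as a caution on the remedy. It is no defence of the paired test.

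**Conclusion.** The point holds: the primary analysis is wrong as written and should be changed before the trial is analysed. A within-patient t-test on a yes/no endpoint does not compare randomised groups, whatever the sample size. How often it would mislead is conditional. Assuming no baseline responders and two-sided testing, the chance of significance with no UC-MSC effect is 1% at n = 10 with 10% background response, 88% at n = 30 with 20%, and over 99% at n = 60 with 20%. A p-value from this test could not support a claim of UC-MSC efficacy.

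**What to change.** First, state in Study design what the control group receives, consistently with the references to randomisation and to two groups.

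Then replace the paired t-test for the primary endpoint with one prespecified comparison. Possible wording: *The primary analysis compares the proportion of patients with overall response at week 24 between the assigned groups, by logistic regression adjusted for baseline proteinuria, and reports the adjusted risk difference with its 95% confidence interval and a two-sided p-value.* Name the single proteinuria measure used as covariate. If the trial will be small, name Fisher's exact test instead, with the unadjusted risk difference and its interval. Fix that choice now, so that it does not depend on the observed counts.

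Reconcile the full analysis set with this. It now drops patients who received no intervention or were never evaluated, which conflicts with analysis by assigned group. Include all patients as assigned and state how a missing week-24 response is counted. Label within-arm paired changes in continuous measures as descriptive.

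If there is no concurrent control, remove the references to randomisation and two groups, report the response rate with an exact confidence interval, and make no efficacy claim from change from baseline.

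Cost: a change of wording, with no extra data if the control group exists. The p-value may be less favourable, and power for the group comparison may be modest, so the planned size should be checked against it.

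### Coagulation, stool and tumour findings are to be tested but are not named or scheduled as outcomes, and a paired t-test does not suit tumour findings if these are new tumours

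*Protocol*

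**What the plan says.** The Protocol's Statistical analysis section states one rule for the safety indicators, the primary endpoint and most secondary outcomes. It illustrates them as "including blood coagulation function, routine tests (blood, urine, and excrement), biochemistry and tumor findings" and says that for all of these "the paired *t*-test will be used to detect any differences". A sentence just before extends the method to every type of variable: "The paired *t*-test will be applied to analyze continuous and categorical variables". The significance threshold is 0.05, with sidedness not stated.

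The section on safety indicators and efficacy endpoints says what is measured. Its safety evaluation has three parts: "Recording of adverse events occurring from the start of subject enrollment until the end of follow-up"; vital signs every 4 weeks for 24 weeks; and "Laboratory tests (including complete blood count, urinalysis, liver function, and blood biochemistry) were tested every 4 weeks for 24 weeks".

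Two further statements in the Statistical analysis section bear on the point. One is that "Descriptive statistics will be used to summarize baseline characteristics, efficacy outcomes, and safety data". The other limits the safety set: "all safety indicators will be obtained from those who have undergone UC-MSC". Item 11 of the exclusion criteria bars a history of malignancy unless it was treated and cured.

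**The concern.** The two sections should describe the same outcomes, and here they do not fully match. A variable that is promised a significance test needs a definition, an assessment and time points. Without them, sites may collect it unevenly or not at all, and the analyst must improvise.

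Tumour findings raise a second problem. In a cell-therapy trial this is a safety question that readers will look for. If the outcome is the appearance of a new tumour, nearly everyone starts without one, and a before-and-after t-test asks only whether the mean change differs from zero. With few events that test can hardly be significant, and a non-significant result says little about how large the risk could be. A report that follows the stated rule could attach a p-value above 0.05 to one, two or three new tumours, which a reader could take as reassurance.

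**Working it through.** **Step 1. Match the items.** The Statistical analysis list has six items when its routine tests are counted separately.

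| Item to be tested | Named in the safety evaluation? |
|---|---|
| Blood (routine) | Yes, complete blood count, every 4 weeks |
| Urine (routine) | Yes, urinalysis, every 4 weeks |
| Biochemistry | Yes, every 4 weeks |
| Coagulation | No |
| Stool | No |
| Tumour findings | No |

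Three of six have no named assessment or schedule. They are not among the secondary efficacy endpoints either. Malignancy is mentioned elsewhere only as an exclusion criterion.

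**Step 2. The paired t-test on new tumours.** There is no figure in the protocol to reproduce. Assumptions: the outcome is a 0/1 indicator, every patient is 0 at baseline (approximately true under exclusion item 11), and the test is two-sided at 0.05. The protocol shown gives no sample size, so n = 20 to 100 is assumed.

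With k new tumours among n patients, the differences are k ones and n − k zeros:

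- mean difference = k/n
- sample variance = k(n − k) / [n(n − 1)]
- t = (k/n) / √(variance/n) = √[k(n − 1)/(n − k)], on n − 1 degrees of freedom

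With k = 0 both the mean and the variance are zero, so t is 0/0 and the test is undefined. With k = 1 the formula gives exactly t = 1 at any n. For n = 40:

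- k = 2: t = √(2 × 39/38) = 1.43
- k = 3: t = √(3 × 39/37) = 1.78
- k = 4: t = √(4 × 39/36) = 2.08

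| New tumours | p, n = 20 | p, n = 40 | p, n = 100 |
|---|---|---|---|
| 0 | undefined | undefined | undefined |
| 1 | 0.330 | 0.324 | 0.320 |
| 2 | 0.163 | 0.160 | 0.158 |
| 3 | 0.083 | 0.083 | 0.083 |
| 4 | 0.042 | 0.044 | 0.045 |

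Four events are needed for p < 0.05 at each n tried, and the p-values barely depend on n. Three tumours among 20 patients and three among 100 therefore give the same p-value, although the observed rates are 15% and 3%.

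**Step 3. How often this would matter.** For an assumed true rate of 2% and n = 40, the chance of at least one tumour is 1 − 0.98^40 = 55%. The chance of at least four, which is what a significant result needs, is 0.8%. At n = 100 the two figures are 87% and 14%.

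**Step 4. Would another paired test help?** No. The exact McNemar test with k changes all in one direction gives p = 0.125 at k = 4 and first falls below 0.05 at k = 6 (p = 0.031). A test of change against zero is the wrong question here; an estimate of the rate is needed.

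**Step 5. What an exact interval shows.** Two-sided 95% Clopper-Pearson limits for an assumed n = 40:

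- 0/40: upper limit = 1 − 0.025^(1/40) = 8.8%
- 3/40 (7.5%): 1.6% to 20.4%

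No events still leaves a rate of nearly 9% compatible with the data, and three events are visibly compatible with about one patient in five. The p-value conveys neither.

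**The case against.** A reader might infer three stronger things, and the document supports none of them.

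- **That the trial will not collect these data.** The laboratory list is introduced as an open one, so coagulation or stool tests may be part of it, and a detailed visit schedule may sit in a document not shown. The text supports only that the three items are not named or scheduled.
- **That the t-test would hide tumours.** A diagnosed tumour would be an adverse event, recorded to the end of follow-up, and safety data are also to be summarised descriptively. A non-significant p-value does not remove a case from those records.
- **That the analysis section is deficient because it does not list complement, SLEDAI-2K, HAQ and the other secondary endpoints one by one.** It refers to most secondary outcomes collectively, and assigning a method to each can be left to a statistical analysis plan.

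The strongest remaining objection is that tumour findings are undefined and stand in a list of laboratory tests. If serum markers on a continuous scale are meant, a paired t-test of change can be computed, and the p-values above do not apply. That stands. It makes the second half of the point conditional, but it also shows that the term needs a definition, and a mean change in a marker would not in itself detect new tumours. Exclusion item 11 also admits patients with a treated and cured malignancy, so the zero baseline is an approximation.

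The unsuitable test for tumours is also one instance of the general rule that applies the paired t-test to categorical variables. It is worth stating separately because event-type safety outcomes need a different remedy, namely estimation.

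**Conclusion.** The point holds in two parts. First, without assumptions: 3 of the 6 variables that the Statistical analysis section lists for testing have no named or scheduled assessment in the section that defines the outcomes, and tumour findings are not defined. A statistical analysis plan could add detail, but the mismatch lies between two sections of the protocol itself.

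Second, conditionally: if tumour findings means new tumours, the stated test is wrong for them. It cannot be computed when there are none, and it cannot reach 0.05 with one to three. This rests on a 0/1 outcome, a baseline close to zero, a two-sided test and an assumed n of 20 to 100, though the choice of n hardly changes the result. The 2% rate is only an illustration.

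The consequence is a p-value that is uninformative and possibly falsely reassuring, together with the lack of a defined tumour assessment. The primary efficacy result does not depend on this. The correction should be made because it concerns how the safety of a cell product is reported.

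**What to change.** 1. Reconcile the two sections. Either name coagulation, stool and tumour assessments in the safety evaluation with their time points, or delete them from the Statistical analysis section.
2. If tumour findings are kept, define the term: new diagnoses, imaging results or serum markers.
3. For new tumours and other event-type safety outcomes, replace the paired t-test with the number and percentage of patients affected and an exact (Clopper-Pearson) 95% confidence interval, plus a listing of cases.
4. Report these in the safety set as now defined, that is, UC-MSC recipients. Report by group only if the safety set is widened to include the comparison group.

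The cost is a wording amendment and a simpler safety table. Keeping the three assessments also means entries in the visit schedule and the data collection forms; deleting them from the analysis text costs nothing further.
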